### Known Potential Benefits

Control participants with negative serum measles IgM and IgG will be provided measles vaccination by the study team or through the national immunization program. All participants with suspected measles will be provided Vitamin A by the study team according to WHO guidelines.[[30](#_ENREF_30)] This treatment replenishes deficient vitamin A levels during measles that occur even in well-nourished children and can help prevent eye damage and blindness as well as reduce mortality.[[30](#_ENREF_30), [31](#_ENREF_31)]

All participants will receive PrEP with Verorab (inactivated rabies vaccine) as part of the study. The WHO rabies PrEP recommendation includes a 2-dose option.[[32](#_ENREF_32)] Because the Sanofi Verorab rabies vaccine package leaflet [[33](#_ENREF_33)] has not yet been updated to include the 2-dose PrEP option and 3 doses is the current approved regimen in each of the proposed study countries, a 3-dose PrEP regimen will be used.

Rabies is estimated to cause 59,000 human deaths annually, and this number is thought to be a gross underestimate of the true burden of this disease. The highest mortality is in Africa with an estimated 21,476 deaths due to dog-mediated rabies each year.[[34](#_ENREF_34), [35](#_ENREF_35)] Because rabies is endemic in the regions where the study will be conducted, provision of rabies PrEP is a benefit to study participation. In the event there is a potential rabies exposure that occurs during the study, participants will be provided with post-exposure prophylaxis (PEP) with HRIG and rabies vaccine.

[figure not shown]

Death rates per capita (per 100 000 population) for dog-mediated rabies. Source :

<https://www.who.int/teams/control-of-neglected-tropical-diseases/rabies/epidemiology-and-burden>

### Assessment of Potential Risks and Benefits

Immune amnesia following MeV infection has the potential to negatively impact health, including an increased risk of serious endemic infections in West Africa, which poses a substantial threat to public health in this region and may disproportionally affect children. The information obtained in this study will contribute to a better understanding of these effects. Study participants will be exposed to minimal risk from biospecimen collection. The risk of vaccination with rabies vaccine is small and therefore outweighed by the potential benefits should a subsequent rabies virus exposure occur, as the vaccination is potentially lifesaving and rabies vaccines and HRIG PEP are often not locally affordable or available.[[36](#_ENREF_36)]

# STUDY OBJECTIVES

The objectives for this study are:

| **OBJECTIVES** | **ENDPOINTS** | **JUSTIFICATION FOR ENDPOINTS** |
| --- | --- | --- |
| **Primary** | | |
| To determine if MeV infection induces a loss of pre-existing immunity (immune amnesia) to endemic pathogens at Week 13 after baseline in children in select African regions. | Mean change in a panel of antibody levels over 13 weeks as measured by multiplex serological methods (e.g. PhIP-Seq/VirScan or SeroChip) and targeted ELISAs for confirmation. | These methods detect antibodies against multiple diverse pathogens and epitopes and assess both neutralizing and non-neutralizing antibodies. |
| To determine the effect of MeV infection on immune response to a controlled immune stimulus (rabies vaccination) at early and late timepoints post-infection. | Proportion of subjects with rabies virus neutralizing antibodies (RVNA) titer ≥ 0.5 International Units per milliliter (IU/mL) as measured by rapid fluorescent focus inhibition test 14 days after the last PrEP regimen vaccination. | These tests will measure the immune response and functionality of antibodies raised against the rabies vaccine. |
|  | Proportion of subjects with an RVNA titer ≥ lower limit of quantification 5-6 weeks after the first rabies vaccine dose. |  |
|  | Geometric mean RVNA titer 5-6 weeks after the first rabies vaccine dose. |  |
| **Secondary** | | |
| To determine if there is an increase in healthcare system encounters in the year following enrollment in children with recent MeV infection compared to those without recent MeV infection. | Mean number of non-study sick visit healthcare system encounters during the 1-year follow-up. | Visits to the healthcare system for sick visits in the year following enrollment in children with recent MeV infection will help determine the clinical impact of the immune amnesia in an objective manner. |
| To determine if MeV infection induces a loss of pre-existing immunity (immune amnesia) to endemic pathogens at Week 52 after baseline in children in select African regions. | Mean change in a panel of antibody levels over 52 weeks as measured by multiplex serological methods (e.g., PhIP-Seq/VirScan or SeroChip) and targeted ELISAs for confirmation. | These methods detect antibodies against multiple diverse pathogens and epitopes. These represent the spectrum of both neutralizing and non-neutralizing antibodies. |
| **Exploratory** | | |
| To assess the appearance and continued production of B and T cells, especially ASCs from PBMCs in circulation following MeV infection in children 1-15 years old in a subset of participants, depending on availability of collected blood samples. | Mean change in cell number and functionality from baseline to 14 days. | Assessing the number and functionality of the B and T cells including ASCs will give insight into the impact of MeV on B cell development and humoral immunity. |
| To attempt to identify the etiology of illness in children who present with signs and symptoms consistent with measles and are screened but not enrolled due to negative measles PCR and IgM. | Unbiased next generation sequencing for pathogen discovery directly from the oropharyngeal (OP)/nasopharyngeal (NP) swab. | This may identify other pathogens that may mimic the clinical presentation of MeV in children who have symptoms but test negative. |
| To identify the genotypes of MeV collected in the study. | Next generation sequencing or targeted Sanger sequencing directly from the OP/NP. | This will allow identification of different genotypes of MeV in the countries enrolling participants. |
| To characterize the phenotype of the rash and/or Koplik spots in children who present with signs and symptoms consistent with measles who test positive for measles (PCR and/or IgM positive) and who test negative for measles (PCR and IgM negative). | Differences in rash patterns/presentation in children who test positive versus those who test negative for measles based on analysis of photographs. | This will allow for a comparison of rash and/or Koplik spot presentation in potential cases that end up testing positive or negative for measles in the laboratory. This will complement the exploratory objective of identifying the etiology via unbiased next general sequencing in the participants who test negative for measles. In addition, we can contribute images of measles rash on dark skinned children and Koplik spots to the medical literature. |

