# PROTOCOL SUMMARY

## Synopsis

| **Title:** | Investigation of Immune Amnesia Following Measles Infection in Select African Regions |
| --- | --- |
| **Study Description:** | This is a prospective, observational, longitudinal study to be conducted in West Africa to investigate the effects of measles virus (MeV) infection on pre-existing immunity, vaccine response, and susceptibility to subsequent illness. Eligible children will be enrolled into 1 of 2 arms: acute MeV infection (cases) or no acute MeV infection (controls) as assessed using upper respiratory specimens and blood samples. Blood samples will be collected at Screening/Enrollment (Day 0), optional repeat IgM serology for inconclusive or negative Day 0 results (Day 7-10), and follow-up visits on Day 14, Week 13, and Week 52. The blood samples will be tested for humoral and cellular immune responses to endemic pathogens to determine changes in antibody diversity and antibody secreting cells (ASCs). All children in each arm will receive rabies vaccination (standard 3-dose series given as pre-exposure prophylaxis [PrEP]), with the first dose randomized to either Week 8 or Week 47 after enrollment. Biological samples will be collected after vaccination to assess if the immune stimulus (rabies vaccine) response differs: 1) between children with and without MeV infection, and 2) based on the timing of the receipt of the rabies vaccine. The study team will collect, to the extent possible, information on healthcare encounters for evaluation and treatment of illness during the year-long follow-up to determine if there is a difference in the number of encounters by study group. |

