| Healthcare Utilization Questionnaire |  |  |  |  |  |  | X | X | X |  |  |  | X |
| Rabies vaccine |  |  |  | (X) | (X) | (X) |  |  |  | (X) | (X) | (X) |  |
| Research blood collection^l^ | X |  | X |  |  |  | X |  |  |  |  |  | X |
| Vitamin A | X^m^ |  |  |  |  |  |  |  |  |  |  |  |  |

Abbreviations: AE, adverse event; HIV, human immunodeficiency virus; Ig, immunoglobulin; MUAC, mid-upper arm circumference; NP, nasopharyngeal; OP, oropharyngeal; PCR, polymerase chain reaction.

(X) = Each participant will receive only one 3-dose series of rabies vaccine according to randomization to early group (vaccination at Visits 2, 3, and 4) or late group (vaccination at Visits 8, 9, and 10).

^a^ EARLY rabies vaccination: Only participants randomized to EARLY rabies vaccine attend Visits 2, 3, 4. Visit 2 occurs 8 weeks after Day 0; Visit 3 occurs 7 days after Visit 2; Visit 4 occurs 21 to 28 days after Visit 2 AND at least 14 days after Visit 3.

^b^ LATE rabies vaccination: Only participants randomized to LATE rabies vaccine attend Visits 8, 9, 10. Visit 8 occurs 47 weeks after Day 0; Visit 9 occurs 7 days after Visit 8; Visit 10 occurs 21 to 28 days after Visit 8 AND at least 14 days after Visit 9.

^c^ Day 0 is defined as the day screening occurs and the first research blood sample is collected. Inclusion/exclusion criteria evaluation for enrollment will be completed when PCR and measles IgG/IgM and HIV results are available, generally by Day 14. In cases where the clinical presentation is consistent with measles but the Day 0 tests (measles PCR and measles IgM) are negative or equivocal, an optional retest of the measles IgM can be done between Days 7 and 10. The guardian/parent will be informed of the need for a retest and asked to bring the child back to the clinic. Blood will be collected via finger stick for the retest and results will be available by Day 14. All potential participants (or guardian/parent) will be informed of eligibility status by a designated study staff by phone, if possible, prior to the Day 14 scheduled study visit or at the Day 14 scheduled study visit. Ineligible participants may be invited to the site to discuss test results and referral for measles vaccination if serum IgG and IgM are both negative.

^d^ Vital signs include temperature, heart rate, and respiratory rate; may be obtained prior to rabies vaccine administration, if clinically indicated.

^e^ MUAC in children 12 to 59 months old.

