# STUDY POPULATION

## Inclusion Criteria

To be eligible to participate in this study, an individual must meet all of the following criteria:

1. Aged 1 to 15 years.
2. Ability of the participant’s legal or culturally acceptable representative to provide informed consent.
3. Ability to give assent, as appropriate.
4. Stated willingness of parent/guardian and participant as appropriate, to comply with all study procedures.
5. Willingness to receive rabies vaccine.
6. Meet the criteria for assignment to Group 1 or Group 2, as follows:
   1. Group 1, cases (acute MeV infection):

- Clinical signs and symptoms suggestive of acute MeV infection (Koplik spots or skin rash) AND
- Laboratory confirmed measles:
  - - - - Upper respiratory specimen (swab) PCR for measles positive.

OR

- - - - - Serum IgM for measles positive.
  1. Group 2, controls (no acute MeV infection):
- No clinical signs and symptoms suggestive of acute MeV infection (Koplik spots or skin rash) AND
  - - - Upper respiratory specimen (swab) PCR negative for MeV AND
      - Serum measles IgM negative AND
      - Serum measles IgG positive and previously vaccinated for measles (2^nd^ dose will be offered if appropriate). If serum measles IgG is negative, participant must be willing to be vaccinated regardless of prior measles vaccine history to meet this criterion.

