### Analysis of Secondary Endpoints

The proportion of participants hospitalized between groups will be reported, exact conditional tests will be performed, and 95% Wilson score CIs will be calculated. A Poisson analysis will be used to compare the number of encounters with medical providers between groups. The average number of encounters per group per person will be calculated and compared. Since each person will have 1 year of follow-up, this would be appropriate. If participants drop out, we will adjust for time in study for each person.

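### The healthcare-encounter endpoint does not separate non-study care for the entry measles episode from later illness, yet the group difference is read as immune amnesia

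*Protocol*

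**What the plan says.** Protocol section 3 (Study Objectives) states the secondary objective as "To determine if there is an increase in healthcare system encounters in the year following enrollment in children with recent MeV infection", compared with children without recent infection. The endpoint is the "Mean number of non-study sick visit healthcare system encounters during the 1-year follow-up". The justification column says that these visits "will help determine the clinical impact of the immune amnesia in an objective manner", and section 4.1 repeats that interpretation.

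The schedule in section 1.3 calls Visit 0 Screening/Enrollment, and footnote c says "Day 0 is defined as the day screening occurs and the first research blood sample is collected". The same footnote says that eligibility is completed generally by Day 14.

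Section 5.1 requires of cases "Clinical signs and symptoms suggestive of acute MeV infection (Koplik spots or skin rash) AND" laboratory confirmation by PCR or IgM. It requires of controls "No clinical signs and symptoms suggestive of acute MeV infection (Koplik spots or skin rash) AND" negative PCR and IgM.

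Section 8.5.3 compares the number of encounters by a Poisson analysis over one year of follow-up per person, adjusting for time in study only for dropouts. It also says "The proportion of participants hospitalized between groups will be reported". Neither comparison has a start point after Day 0, a lag or a restriction by cause. The Healthcare Utilization Questionnaire is scheduled at Weeks 13, 26, 39 and 52; its recall period and content are not given.

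**The concern.** At the start of counting the groups differ in two ways: cases have had measles, which is the exposure of interest, and cases are ill with it at that moment. Immune amnesia is a claim about what follows the acute illness. Section 2.2 keeps the two apart: it describes a lasting impact in addition to acute disease, and cites morbidity effects beyond those of the acute disease alone. The endpoint merges them.

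Any non-study return visit, admission or acute complication belonging to the entry episode is counted for a case, and controls have no measles episode to match it. The bias therefore runs towards the hypothesis. A positive result could reflect the acute illness, its after-effects or both, and the planned analysis could not tell which. The comparison of the proportion hospitalized has the same weakness.

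Section 8.2 calls healthcare encounters a particularly important secondary endpoint, and it is the study's clinical test of amnesia. Safety data cannot be relied on to separate the two later, because section 7.2 leaves events due to the natural course of the disease out of adverse event recording.

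**Working it through.** **The plan's own figure.** Section 8.2 states 90% power for 0.5 (control) versus 0.7 (measles) with at least one medical visit. I used the pooled two-sample test of proportions. The two-sided 0.05 level is an assumption here, because the document states it for the rabies analysis and not for this calculation.

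- 128 per group (256 in total): power 0.909.
- 120 per group (about 240 evaluable; 256 is said to cover 6.5% loss): power 0.890.

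The stated 90% reproduces, so the power arithmetic is not at fault. The question is what the test would be detecting.

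**Inputs that are assumptions.** The document gives no rate of care for the entry episode and no background encounter rate. I therefore assume no amnesia effect at all, 120 per group, and a range for each unknown.

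**Counts (Poisson).** Let m be the control mean per year and e the extra index-measles encounters per case.

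- Apparent rate ratio = (m + e)/m.
- Standard error of the difference in means = √((2m + e)/120).
- Rejection probability ≈ 1 − Φ(1.96 − e/SE).

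Example with m = 1.5 and e = 0.25: SE = √(3.25/120) = 0.165, e/SE = 1.52, and 1 − Φ(0.44) = 0.33.

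| Extra encounters per case, e | m = 0.7 | m = 1.5 | m = 3.0 |
|---|---|---|---|
| 0.25: rate ratio | 1.36 | 1.17 | 1.08 |
| 0.25: rejection | 0.57 | 0.33 | 0.19 |
| 0.5: rate ratio | 1.71 | 1.33 | 1.17 |
| 0.5: rejection | 0.98 | 0.83 | 0.57 |
| 1.0: rate ratio | 2.43 | 1.67 | 1.33 |
| 1.0: rejection | >0.99 | >0.99 | 0.985 |

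**Any visit.** Let p0 be the control proportion and q the share of cases with at least one non-study visit for the entry episode, independent of other visits. Then p1 = p0 + (1 − p0)q, tested as above. With the Protocol's p0 = 0.5:

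| q | Case proportion p1 | Rejection probability |
|---|---|---|
| 5% | 0.525 | 0.07 |
| 10% | 0.55 | 0.12 |
| 20% | 0.60 | 0.34 |
| 30% | 0.65 | 0.65 |
| 40% | 0.70 | 0.89 |

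At q = 40%, p1 = 0.5 + 0.5 × 0.4 = 0.70, which is the whole planning difference. At q = 20%, rejection is 0.61 if p0 = 0.3 and 0.18 if p0 = 0.7. The nominal value throughout is 0.05.

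**The case against.** Several points on the other side are sound.

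- **Study visits do not count.** The endpoint is limited to non-study visits, so the Day 0 and Day 14 study visits are excluded. A reader might infer that the measles episode as a whole is counted. It is not; only additional outside care for it from Day 0 can be.
- **The start point is not fully settled.** Eligibility is completed generally by Day 14 (section 1.3), eligibility tests must precede enrollment (section 7.1.2), and section 8.3 ties enrollment to Day 14 confirmation. If enrollment means that confirmation, the overlap shrinks. It is not excluded, and the schedule and Synopsis point to Day 0.
- **The questionnaire is not shown.** A reader might take the Week 13 form as covering Day 0 to Week 13 and lacking dates or reasons. That is inference; the fields may already exist.
- **Controls may be ill.** They must be free of measles signs and positive tests, not of all illness, so their early count need not be zero.
- **The size is unknown.** A reader might infer that the objective would very likely be met with no after-effect at all. That fails at the lower end of the range: 33% and 19% at two of the three baselines with 0.25 extra encounters, and 12% if one case in ten has such a visit.
- **It is a secondary endpoint.** Both primary objectives are untouched, and hospitalization is an analysis in section 8.5.3, not an endpoint listed in section 3.

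It can also be said that the objective literally concerns encounters in the year, which the endpoint measures, and that lag rules are commonly left to an analysis plan. This is less persuasive. The Protocol itself fixes both the one-year window and the amnesia interpretation, and no later analysis can separate encounters whose date and reason were not recorded.

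**Conclusion.** The concern holds in a limited form. Non-study care for the entry measles episode is not separated from later illness, in either the encounter count or the proportion hospitalized, while section 3 reads the difference as the clinical impact of immune amnesia. The direction of the bias favours the hypothesis.

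Its size cannot be obtained from the document. Under the assumed ranges of 0.25 to 0.5 extra encounters per case and 0.7 to 3.0 background encounters per year, the false-positive probability runs from about 19% to 98%. On the any-visit scale, with a control proportion of 0.5, it runs from 7% to 89% as the share of cases with such a visit rises from 5% to 40%. These figures assume no amnesia effect, 120 per group, Poisson variation for the counts, and independence of index-measles and other visits on the any-visit scale. They support a possibly substantial inflation, not a near-certain false positive. Severity is should-fix, as a cheap improvement to a secondary endpoint.

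**What to change.** In sections 3 and 8.5.3:

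1. Base the immune-amnesia comparison on encounters, hospitalizations and person-time from a pre-specified landmark after the acute phase, the same in both groups. Week 4 is one example, with Day 14 and Week 8 as sensitivity analyses. The document does not dictate the choice, so the sponsor should justify it.
2. State whether the year is counted from Day 0 or from the Day 14 eligibility confirmation.
3. Ensure that the date and reason of each encounter are recorded, if the questionnaire does not already do so. If dates are unavailable, count from Week 13 using the Week 26, 39 and 52 questionnaires.
4. Report encounters, deaths and dropouts before the landmark separately by group.
5. Keep the full-year count alongside, described as the total burden of measles and not as amnesia alone.

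The cost is a change of wording and possibly two fields on a form. With a Week 4 landmark, 4 of 52 weeks (4/52 = 7.7%) leave the main comparison, including some early secondary infections that may belong to the effect of interest. The comparison also conditions on remaining in follow-up to the landmark. Items 4 and 5 are there to make both losses visible.

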# STUDY DESIGN

## Overall Design

This is a prospective, observational, longitudinal study to be conducted in select African regions to investigate the effects of MeV infection on pre-existing immunity, immune response to a known controlled immune stimulus (rabies vaccine), and susceptibility to infection to prevalent pathogens. Although children will receive the rabies vaccine as part of this study, we consider this an observational study rather than an interventional study. An interventional study tests an outcome of that intervention, e.g., efficacy or safety. The rabies vaccine is not used as a research intervention in this sense, i.e., we are not testing the efficacy or safety of the rabies vaccine, but rather using the vaccine as an immune stimulus to understand the effect of measles immune amnesia over time. In other words, the rabies vaccine is not the object of this investigation, but merely a means to allow assessment of the research objectives. Other vaccines could be used for this purpose, but rabies vaccine is convenient because there will not be pre-existing immunity to confound the results. The study is expected to take place in a subset of the NIAID Division of Clinical Research (DCR) Special Projects sites and any additional site(s) that may be identified. Specific study sites within each country will be in areas experiencing measles outbreaks.

We will enroll approximately 256 children aged 1-15 years into study Group 1 (acute MeV infection) or Group 2 (no acute measles infection). See section 5.1 for specific group criteria. In each group, approximately half of the enrolled participants will be ages 1-5 years and approximately half will be ages 6-15 years. Group 2 will be matched to Group 1 on gender and catchment area of study implementation.

Participants will undergo blood collection for screening and research testing at Day 0, between Days 7 and10 (optional, if Day 0 measles PCR and IgM are negative or equivocal in a child that presents with signs and symptoms consistent with measles), Day 14, Week 13, and Week 52. An upper respiratory specimen for MeV PCR will be collected at Day 0. Urine will be collected from females of reproductive potential to check for pregnancy at study visits with rabies vaccination or research blood collection. Hemoglobin levels will be checked at each study visit prior to research blood collection. Research samples will be tested for humoral and cellular immune responses to rabies vaccination (used as a controlled immune system stimulus, see section 8) and other research testing as described below (section 7.3). In addition, targeted sequencing will be performed on the measles virus to identify specific genotype. Unbiased sequencing will be used to try to identify the etiology in participants who have signs and symptoms consistent with measles but who test negative for measles by PCR and IgM. Optional photographs will be taken of the rash and/or Koplik spots at Day 0 to characterize the phenotype of the participants who test positive or negative for measles. We will also collect information on healthcare system encounters throughout the study period to help determine the clinical impact of immune amnesia after measles infection.

Participants with acute measles at screening/enrollment will be provided vitamin A treatment if they have not previously received it as part of their treatment. The treatment will follow WHO guidelines: 2 doses of 200,000 IU to be taken orally, 24 hours apart. The first dose will be given at the screening/enrollment visit, and the second dose will be given to the parent/guardian to be given the following day. A participant who has a rabies exposure during study participation will be provided rabies PEP with HRIG and rabies vaccine according to standard practice and the approved Verorab dosing schedule and depending on PrEP status. Any participant who receives rabies PEP prior to the timepoint that they were scheduled (randomized) to receive rabies PrEP under this study will continue in the study for follow-up visits but not receive PrEP according to their assigned randomization schedule. Data from these participants will be analyzed as described in Section [8.3](#_Population_for_Analysis).

Each site will have site-specific processes described in the manual of procedures (MOP) for activities, including but not limited to recruitment of cases and controls, informed consent and assent processes, laboratory processes, instructions for study procedures, and processes for follow-up of those with suspected MeV infection, HIV counseling and testing, and pregnancy testing.

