## Exclusion Criteria

An individual who meets any of the following criteria will be excluded from participation in this study:

1. HIV infection or any other immunosuppressive condition or medications.
2. Pregnant or lactating.
3. History of prior measles or immunologic evidence of prior measles in the absence of prior measles vaccination.
4. Severe anemia, defined as hemoglobin less than 8 g/dL.
5. Any acute or chronic condition which, in the opinion of the investigator, constitutes a contraindication to participation in this study.

**Co-enrollment guidelines:** Co-enrollment in other trials is restricted, other than enrollment on observational studies that do not exceed blood collection volume limits. Study staff should be notified of current and planned co-enrollment on any other protocol as it may require the approval of the principal investigator (PI).

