## Sample Size Determination

The overall sample size will be 256 participants. We will accrue 128 acute measles participants (with half of these in age group 1-5 years and half in age group 6-15 years) and 128 control participants (with half in each age group).

Randomization to early and late rabies vaccine will be stratified by country, group, and age.

Power for comparison of rabies titers

The sample size calculation is based on detecting a difference in the rabies antibody geometric mean titer between the MeV and control groups. The rabies vaccine will be given to half of the participants at Week 8 and half at Week 47 post enrollment, and the rabies antibody titer will be measured 5-6 weeks after receipt of the first vaccine dose (Weeks 13 and 52, respectively). There will be a random assignment for receipt of rabies vaccination to the two timepoints with equal numbers in the acute measles young and old groups and control young and old groups. In this analysis only one measurement of rabies antibody titer per participant will be included and it will be the measurement 5 weeks after receiving the rabies vaccine.

The total study sample size will be divided into 8 cohorts stratified by measles status, age group, and rabies vaccine timepoint as outlined in Figure 1. The standardized difference that can be detected with 90% power using a 0.05 level two-sided test for different sample sizes by specific cohort are shown in [Table 2.](#_Table_2:_Standardized)

Table 2: Standardized detectable difference with 90% power using a 0.05 level two-sided test for different sample sizes.

| Sample size per specific cohort (total study sample size) | Comparison of MeV to control at either the early time point or late time point  (assume std=1) | Interaction between time and group.  Example: comparison of difference between early MeV and control vs late MeV and control  (assume std=(1^2^+1^2^)^.5^=1.4) |
| --- | --- | --- |
| 20 (160) | 1.05 | 1.47 |
| 30 (240) | 0.85 | 1.19 |
| 40 (320) | 0.73 | 1.02 |

The chosen sample size of 256 accounts for a 6.5% loss to follow up.

Power for multiplex serological methods for global antibody analysis (e.g. virscan):

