## Population for Analysis

All participants enrolled in the study will be analyzed. Any control participants who later becomes infected with measles or participants from either group that become pregnant will be censored at the time of infection or pregnancy.

If a participant who was enrolled as a case is later diagnosed with measles during the study, there is no change with regards to how their data will be analyzed or with regards to other study procedures. However, as a measles infection should confer lifelong immunity, this scenario is expected to be extremely unlikely.

A participant who has received rabies PEP during the study prior to the timepoint at which they were scheduled (randomized) to receive rabies vaccination will be excluded from the primary analysis of the rabies vaccine but included in the immune amnesia analysis.

Participants who have received their first dose of rabies PrEP as scheduled (randomized) will be analyzed as planned.

Participants who do not receive a full course of rabies vaccine will be included in all analyses. A sensitivity analysis will be performed where these participants are excluded.

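### The protocol takes absence of prior rabies immunity as given, but no eligibility or analysis rule secures it for the RVNA comparison

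*Protocol*

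**What the plan says.** Section 4.1 chooses rabies vaccine as the controlled stimulus on the ground that "rabies vaccine is convenient because there will not be pre-existing immunity to confound the results". Section 2.3.2 describes the setting: "Because rabies is endemic in the regions where the study will be conducted".

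The only rabies-related entry criterion in section 5.1 is "Willingness to receive rabies vaccine". Section 5.2 lists five exclusions. The one on immune status is "HIV infection or any other immunosuppressive condition or medications", and none concerns earlier rabies vaccine, PEP or rabies immune globulin (HRIG).

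The three RVNA endpoints in section 3 are all post-vaccination values: two threshold proportions and a geometric mean titre (GMT). Section 8.2 adds: "In this analysis only one measurement of rabies antibody titer per participant will be included".

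Section 8.4 analyses everyone enrolled. It drops from the primary rabies analysis, but not from the immune-amnesia analysis, a child who had PEP during the study before the randomised vaccination time. It then says: "Participants who have received their first dose of rabies PrEP as scheduled (randomized) will be analyzed as planned". Under section 4.1, a child exposed to rabies during the study "will be provided rabies PEP with HRIG and rabies vaccine", subject to standard practice, the approved dosing schedule and PrEP status.

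General vaccination history is taken at screening and updated (7.1.2, 7.2). Plasma from the research draws, which include Day 0, is kept partly for rabies antibody (7.3).

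**The concern.** The rabies objective reads the titre about five weeks after dose 1 as a response to a new antigen. In a child already vaccinated it is a booster response. In a child given PEP between dose 1 and the draw it includes extra vaccine and possibly passive antibody. The plan already treats PEP before the scheduled dose as disqualifying for this analysis. The same reasoning covers vaccine or PEP received before enrolment, which the rule does not reach.

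Measles status is not randomised, and controls are matched only on gender and catchment area. IgG-positive controls must have been measles-vaccinated and cases need not have been, so the groups could differ in access to vaccination generally. An uneven share of previously vaccinated children would bias the GMT contrast. An even share would add variance, and such children would tend to count as responders in both threshold endpoints. The study also hypothesises that measles erodes antibody from earlier vaccinations, so in a primed child a titre difference could reflect lost memory rather than an altered new response.

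**Working it through.** **1. The plan's own figure.** Table 2 (section 8.2) uses 90% power, a two-sided 0.05 test and SD 1. A two-sample t-test gives detectable differences of 1.052, 0.851 and 0.734 for 20, 30 and 40 per cohort, against 1.05, 0.85 and 0.73 stated. The table reproduces. At d = 0.85 and n = 30 the power is 0.899.

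**2. Inputs.** From the protocol: n = 30 per cohort, d = 0.85, alpha 0.05 two-sided, SD 1. Assumed, because the protocol gives no figures: the table's unit is one ln-titre unit, a share p of children is previously vaccinated, and their titres are F = 5 to 10 times higher (ln 5 = 1.609, ln 10 = 2.303).

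**3. Equal prevalence in both groups: loss of power.** SD = sqrt(1 + p(1 − p)(ln F)²), and the effective difference is 0.85/SD. For p = 0.05 and F = 5: SD = sqrt(1 + 0.0475 × 2.590) = 1.060, difference 0.802, power 0.863.

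| p | SD, F = 5 | SD, F = 10 | Power, F = 5 | Power, F = 10 |
|---|---|---|---|---|
| 0.01 | 1.013 | 1.026 | 0.892 | 0.884 |
| 0.02 | 1.025 | 1.051 | 0.885 | 0.869 |
| 0.05 | 1.060 | 1.119 | 0.863 | 0.825 |
| 0.10 | 1.110 | 1.215 | 0.830 | 0.759 |

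These powers let previously vaccinated children show the full measles effect. If they show none, the difference becomes 0.85(1 − p)/SD, and power falls to 0.827-0.785 at 5% and 0.747-0.669 at 10%.

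**4. Unequal prevalence: bias.** If the share differs between groups by δ, the ln-GMT difference shifts by δ × ln F and the GMT ratio by F^δ, with no measles effect.

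| δ | Ratio, F = 5 | Ratio, F = 10 |
|---|---|---|
| 0.01 | 1.016 | 1.023 |
| 0.02 | 1.033 | 1.047 |
| 0.05 | 1.084 | 1.122 |
| 0.10 | 1.175 | 1.259 |

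The largest shift, 0.10 × 2.303 = 0.230, is 27% of the detectable 0.85. At δ = 0.02 and F = 10 it is 0.046, or 5%.

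**5. PEP after dose 1.** Dose 1 is at Week 8 or Week 47 and the draw at Week 13 or Week 52, so the window is about five weeks. The protocol gives no exposure rate, so this part cannot be sized. That these children are kept follows from the wording of 8.4, which does not name the case.

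**The case against.** Section 2.3.3 says that rabies vaccine and HRIG are often unaffordable or unavailable locally. This points to low prior vaccination and gives the statement in 4.1 some support. At 1-2% prevalence the loss of power is small. Matching on catchment area and balancing by age group make a large imbalance less likely. Keeping children who started PrEP as randomised is also a defensible inclusive choice. All of this stands. It limits the size but does not supply the missing rule.

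Three stronger readings are tempting, and the documents do not support them.

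- A reader might infer that prior immunity is not measured at all, or that a booster response could never be recognised. Vaccination history is recorded, Day 0 plasma is stored, and the single-titre sentence describes what enters the comparison without barring other assays. The gap is that no stated rule uses these data.
- A reader might infer that every child given PEP after dose 1 receives HRIG. PEP content depends on PrEP status, so passive antibody is possible but not established.
- A reader might infer that the measles contrast is in fact biased, or that endemic rabies means prior immunity is common. Bias needs unequal prevalence, and the protocol gives no prevalence for either group.

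**Conclusion.** The point holds in limited form. An assumption on which a primary objective rests is stated as fact, and the eligibility criteria and section 8.4 do not secure it. Followed exactly, the plan would count booster antibody, and antibody from PEP after dose 1, as response to the study series.

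The effect may be negligible or material. Power is about 0.87-0.89 at 1-2% prevalence, 0.82-0.86 at 5% and 0.76-0.83 at 10%. The spurious shift in the GMT ratio is about 2-5% for a 1-2 point imbalance and 8-26% for 5-10 points. These ranges rest on the assumed fold-rise, SD and prevalence, and the protocol's remark on access favours the lower end. The change is worth making because it extends a rule the plan already applies and uses data already collected.

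**What to change.** In section 8.4:

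1. Extend the existing PEP exclusion so that children with documented rabies vaccine, PEP or HRIG before enrolment are left out of the primary RVNA analyses and kept in the immune-amnesia analyses. The vaccination history taken at screening would need to record rabies products explicitly.
2. Add a sensitivity analysis that excludes titres drawn after PEP given between dose 1 and the draw.
3. As an optional check, run RVNA on stored Day 0 plasma in all groups and repeat the analysis without children at or above the lower limit of quantification. Week 13 plasma should not be used for the late group. The antibody loss the study hypothesises could by then push a previously vaccinated measles case below the limit while a comparable control stays above it, so exclusion would depend on measles status.

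The cost is a few children lost from the RVNA analysis. The optional check also uses some stored plasma, which is limited because each draw is at most 5 mL and serves other assays. No dose, schedule or PEP practice changes.
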